#### Process evaluation measures

2.9.1

##### Before the intervention

2.9.1.1

As part of the onboarding process – to prepare employee and managerial participants for the intervention and determine their readiness for such a study – the first process measurement will be administered. This process measurement will capture elements central to participants’ buy-in (i.e., participants’ readiness for change and communication). These and subsequent process measures will be drawn from the Intervention and Multiphase Training Transfer Assessment Questionnaire (IMTTAQ; Vasquez et al., 2026), a validated instrument that assesses contextual factors, transfer mechanisms, and behavioral outcomes across the pre-training, during-training, and post-training integration phases of occupational health training interventions. Examples of the items are “*I am ready to accept the changes brought about by the intervention*” [readiness for change; four items, adapted from Randall et al. (2009)] and “*I have received information about the goals of the intervention*” (communication; three items). These will be measured on a five-point Likert scale, ranging from 1 (strongly disagree) to 5 (strongly agree).

It will, furthermore, also be important to determine participants’ degree of job resources (i.e., autonomy) and job demands (i.e., workload). Example items are “*I am given a lot of freedom to decide how to do my own work*” and “*I never seem to have enough time to get everything done in my job*” [NIOSH Worker Well-Being Questionnaire (WellBQ)] (Chari et al., 2024). These two items will be measured on a four-point Likert scale, ranging from 1 (strongly disagree) to 4 (strongly agree). These two, as well as the above seven items, will be collected at T1 (Groups 1, 2, and 3) and again at T3 (Group 3) (see Figure 1).

##### During the intervention

2.9.1.2

On the day of the workshop, a survey to determine the level of voluntary participation (single item), integration (three items; participants’ willingness to use what they have learnt; i.e., intention to transfer), training design (four items; transferability to the job), acceptability of the content (three items; effectiveness of materials and methods in facilitating participant learning), and the need supportiveness of the facilitator (eight items) will be administered. Participants will be asked whether they were allowed to participate voluntarily in the study, with responses to “*My participation in this intervention is voluntary*” ranging from 1 (strongly disagree) to 5 (strongly agree). Other examples include “*I believe what I learned in the training can help me at work*” (integration), “*It is clear to me that the trainer conducting the training understood how I will use what I learn*” (training design), and “*I feel the training met my expectations*” (acceptability of content) (Vasquez et al., 2026). This will be measured at T2 (for Groups 1 and 2) and T4 (for Group 3), directly after participants have received the intervention training. The trainer’s need-supportiveness will be measured through an adapted version of the Tripartite Measure of Interpersonal Behaviors-Supervisor (TMIB-S) (Huyghebaert-Zouaghi et al., 2023). Examples of items include “*The facilitator showed that he understands my perspective*” (autonomy support), “*The facilitator recognized my efforts and accomplishments*” (competence support), and “*The facilitator showed care and concern*” (relatedness support). Participants will rate these behaviors on a seven-point Likert scale, ranging from 1 (strongly disagree) to 7 (strongly agree).

##### Implementation

2.9.1.3

After participants have had 2 weeks to implement their need crafting and need-support plans, a follow-up meeting will be arranged to measure participants’ opportunities to integrate (three items; tasks/situations needed for application), training transfer (three items; the frequency with which they apply new skills), and peer support (three items; support in applying the newly acquired skills and knowledge). Measured at T3 and T5, respectively (see Figures 1, 2), the survey will contain nine items and will be rated on a five-point Likert scale, ranging from 1 (strongly disagree) to 5 (strongly agree). Examples include “*I had access to the necessary resources to implement my need crafting plan*” (opportunities to integrate), “*I successfully applied the need crafting strategies from training in my daily work*,” and “*My colleagues asked if I had problems or trouble at work*” (Vasquez et al., 2026). Lastly, participants will be asked to share their experiences (through open-ended questions in a focus group setting) regarding the effectiveness of the implementation process and how they can ensure that the need crafting actions are sustainable and provide prolonged implementation and learning (i.e., “*What made it difficult to implement your need crafting plan?*”, “*What did you learn?*”, “*What would you regard as a developmental area for yourself?*”, and “*What was surprising for you?*”).

##### Follow-up

2.9.1.4

Lastly, 1 month after the intervention training, participants will be required to reflect on the month that followed the intervention training and complete the same nine-item process measure as at the time of the 2-weeks reflection meeting. However, this time, an electronic version of the open-ended survey will be distributed to participants and measured at T4 and T6, respectively (see Figures 1, 2).

The IPEF will help ensure a cost-effective process evaluation through its expansive approach. The quantitative process measures also align with the validated temporal structure of the IMTTAQ (pre-training, during training, and training integration), supporting comparability with other multilevel occupational health interventions (Vasquez et al., 2026). By means of this approach, quantitative process evaluation will be done through the continuous collection of information throughout the study and follow-up questionnaires after the study (Nielsen et al., 2023). Quantitative evaluation can also be enhanced through qualitative semi-structured interviews to gather the perceptions and experiences of participants about the intervention (Abildgaard et al., 2016). The current study will primarily apply quantitative process evaluation, as it allows for standardized measures to be used. Such measures reduce the time for data collection. Quantitative process evaluation is equipped for statistical analysis and explanation of variances in outcomes, offers more breadth and representativeness of the population, and can be done at multiple intervention levels (Abildgaard et al., 2016; Randall et al., 2009). Quantitative data will be collected at both the individual and leader levels of the IGLO. However, qualitative data collection methods may be deployed for evaluation purposes in instances where discrete contextual or unexpected events may have occurred during the intervention (Nielsen et al., 2023).

To integrate process evaluation and outcome evaluation, Nielsen et al. (2023) advise that the different elements of the intervention be measured more than once during the intervention and, subsequently, analyzed to determine the influence these elements have on each other.

### Proposed integration of effect and process evaluation

2.10

To ensure a comprehensive evaluation, the planned study will integrate effect evaluation with a realist-informed process evaluation. The evaluation of the effect will focus on whether the intervention yields the anticipated improvements in need crafting, perceived leader support, and need satisfaction, as well as whether these changes differ between groups over time. Complementing this, the realist evaluation will be used to explore how and why such outcomes may emerge, for whom they are most salient, and under what contextual conditions they are likely to occur.

#### Context, mechanism, and outcome theoretical framework

2.10.1

From a critical realist evaluation perspective, it is not enough to state whether an intervention was successful; it is also necessary to understand why it worked or did not work, for whom, and under what circumstances (Abildgaard et al., 2016; Nielsen and Abildgaard, 2013; Roodbari et al., 2023). Such testing and evaluation of organizational interventions and their specific working mechanisms in certain contexts to yield specific outcomes are done by developing and testing context-mechanism-outcome (CMO) configurations (Nielsen and Abildgaard, 2013; Roodbari et al., 2023). The first of the three elements comprising the CMO is context: the context and environment in which the intervention occurs, which can include employees’ perceptions about the intervention, the organizational setting and culture, or available resources; these all influence how the intervention works. The second element is mechanism: the processes that are triggered and activated because of the intervention and how participants, ultimately, interpret and respond to the intervention, which drives the change. The third element is outcome, which refers to the outcomes – both anticipated and unexpected – that arise when certain mechanisms are activated in certain contexts (Roodbari et al., 2023).

#### Proposed context-mechanism-outcome configurations

2.10.2

Guiding the protocol are preliminary program theories articulated as CMO propositions, which set out the circumstances under which intervention mechanisms are expected to be activated and produce outcomes. Context will be conceptualized as omnibus (relatively stable, broad organizational features such as workload, autonomy, or managerial participation) and discrete (situational, time-bound, and concurrent events such as fluctuating colleague support). Mechanisms will be framed as participants’ interpretations and behavioral responses (e.g., perceived relevance, opportunities for transfer, or sense of support). At the same time, outcomes will be distinguished between proximal indicators (need crafting behaviors and perceived leader support) and distal indicators (basic psychological need satisfaction).

Table 3 presents the configuration of potential CMO families that will be explored in the intervention study. The table organizes the measured variables (from Figure 1) into five higher-order families to provide a holistic framework for understanding how the intervention is expected to function. For each family, relevant contexts (e.g., readiness for change, job resources, colleague support, and trainer behaviors) are specified as the conditions within which the intervention unfolds. These contextual features are expected to trigger specific mechanisms, captured through participants’ responses such as voluntary participation, training transfer, engagement with need crafting, or perceived intervention effectiveness. When these mechanisms are activated in particular contexts, they are hypothesized to generate proximal outcomes (i.e., need crafting behaviors and perceived leader support), which, in turn, contribute to the distal outcome of basic psychological need satisfaction. This structuring highlights how different aspects of the organizational setting and intervention delivery may interact with participants’ interpretations to produce both immediate and longer-term effects.

**TABLE 3 T3:** Context-mechanism-outcome (CMO) families for the intervention study.

CMO family	Contexts	Mechanisms	Outcomes
1. Organizational readiness and communication	- Readiness for change - Communication	- Voluntary participation - Integration (willingness to use learning)	Proximal: perceived leader support Distal: need satisfaction
2. Work environment (resources and demands)	- Job resources (autonomy) - Job demands (workload)	- Training transfer (employee)	Proximal: need crafting behaviors Distal: need satisfaction
3. Social support dynamics	- Colleague support	- Training transfer (employee)	Proximal: perceived leader support and sustained need-supportive behaviors Distal: need satisfaction
4. Training design and delivery	- Training design - Acceptability	- Integration (willingness) - Training transfer (employee and manager, as applicable)	Proximal: need crafting behaviors Distal: need satisfaction
5. Trainer facilitation	- Trainer need-supportive behaviors	- Voluntary participation - Integration (willingness)	Proximal: need crafting behaviors Distal: need satisfaction

These program theories will guide the subsequent statistical analyses by offering testable propositions about both the impact of the intervention and the contextual factors shaping its effectiveness.

#### Statistical integration plan

2.10.3

Data will be analyzed to examine how contextual conditions interact with mechanisms to generate proximal and distal outcomes. Descriptive statistics will, firstly, be used to summarize baseline characteristics of participants and study variables. Reliability analyses will be conducted for all multi-item scales. Missing data will be handled using full information maximum likelihood (FIML), and sensitivity analyses will be conducted to assess the robustness of findings. Where appropriate, effect sizes and confidence intervals will be reported alongside statistical significance.

For CMO analyses, moderation models will be estimated to test whether contextual variables (e.g., readiness for change, communication, autonomy, workload, colleague support, training design, and trainer behaviors) influence the strength of relationships between the intervention and mechanisms (e.g., voluntary participation, training transfer, and engagement with need crafting). In turn, mediation models will be used to examine whether mechanisms predict proximal outcomes (need crafting behaviors and perceived leader support), which then lead to the distal outcome (basic psychological need satisfaction).

The qualitative data collected from the focus groups and online surveys will undergo conventional content analysis where textual data will be used to inductively develop categories and themes that best describe the data (Hsieh and Shannon, 2005). After keywords and themes have been identified, interpretation of the context will occur (Abildgaard et al., 2016). Qualitative themes will be linked to the five CMO families to confirm or expand mechanisms.

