As process evaluation will occur continuously throughout the entirety of the intervention study, fidelity measurement will be conducted through the process evaluation to determine the potential impact that various factors have on the study outcomes. Such factors include the delivery of the intervention, the degree of implementation of need crafting activities by participants, whether participants have been allowed to participate in need crafting, how useful participants have found need crafting, and whether they have, in fact, engaged with need crafting once back at their jobs (Randall et al., 2009; Spacey et al., 2019).

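### The planned context moderation of the intervention-to-mechanism path has no untrained comparison: for mechanisms, only NC + NN versus the self-selected NC-only group can be contrasted

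*Protocol article*

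**What the plan says.** Section 2.10.3 (Statistical integration plan) specifies moderation models to test whether contexts "influence the strength of relationships between the intervention and mechanisms (e.g., voluntary participation, training transfer, and engagement with need crafting". It lists seven contexts: readiness for change, communication, autonomy, workload, colleague support, training design and trainer behaviors. Table 3 adds acceptability as a context and integration as a mechanism. Section 2.10.3 does not say which contrast the intervention stands for.

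The measurement schedule is in section 2.9.1:

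- Readiness, communication, autonomy and workload "will be collected at T1 (Groups 1, 2, and 3) and again at T3 (Group 3"), before training.
- For the workshop-day survey, which covers voluntary participation, integration, training design and acceptability: "This will be measured at T2 (for Groups 1 and 2) and T4 (for Group 3), directly after participants have received the intervention training".
- On the same day, "The trainer’s need-supportiveness will be measured through an adapted version of the Tripartite Measure of Interpersonal Behaviors-Supervisor (TMIB-S"). This is the Table 3 context "Trainer need-supportive behaviors".
- For opportunities to integrate, training transfer and peer support: "Measured at T3 and T5, respectively (see Figures 1, 2), the survey will contain nine items".
- One month after training (T4 for Groups 1 and 2, T6 for Group 3), participants "complete the same nine-item process measure as at the time of the 2-weeks reflection meeting".

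Engagement with need crafting appears in section 2.9 as a fidelity question, "whether they have, in fact, engaged with need crafting once back at their jobs". Section 2.9.1 names no separate scale for it.

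**The concern.** To ask whether a context changes the effect of the intervention on a mechanism, the mechanism must be observed under at least two intervention conditions, and the context should not itself be a product of the intervention. The schedule meets the first requirement only for NC + NN against NC only. It fails the second for about half of the contexts.

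For whom and under what conditions the program works is a headline aim of the article. If the step is run as worded, readers could take one of two things for context moderation of a training effect: a comparison driven by which managers volunteered, or associations among ratings given in one survey by trained people.

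**Working it through.** No stated figure needs reproducing. The check sets the schedule against the model.

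**Schedule by training status (sections 2.9.1.1 to 2.9.1.4)**

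| Variable | Role | Groups 1 and 2 | Group 3 | Untrained values |
|---|---|---|---|---|
| Readiness, communication, autonomy, workload | context | T1 | T1, T3 | yes |
| Training design, acceptability, trainer behaviors | context | T2, after training | T4, after training | none |
| Colleague (peer) support | context | T3, T4 | T5, T6 | none |
| Voluntary participation, integration | mechanism | T2, after training | T4, after training | none |
| Training transfer | mechanism | T3, T4 | T5, T6 | none |

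**Step 1: training versus no training.** The model is M = b0 + b1·A + b2·C + b3·(A×C), where M is the mechanism, A the intervention and C the context. If A means trained versus untrained, A = 1 on every row that has a value of M. The column for A then equals the intercept, and A×C equals C. The design matrix has rank 2 of 4. Only b0 + b1 and b2 + b3 can be estimated; b3, the moderation, cannot.

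**Step 2: the randomized contrast.** Group 3 is the control only until it is trained (section 2.1). In that period its process items are the four in the first row. By the time it supplies any mechanism value it has received the same NC + NN as Group 1, and the two groups differ only in timing.

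**Step 3: the contrast that remains.** If A means NC + NN (Group 1, or Groups 1 and 3) versus NC only (Group 2), the rank is 4 of 4 and b3 is identified. It describes moderation of the added manager component. Group 2 is formed from departments whose managers do not volunteer.

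**Step 4: precision of that contrast.** Assume a residual SD of 1, a context SD of 1, independent observations and an interaction of 0.4 SD per SD of context. None of these values comes from the article. The standard error of b3 is about sqrt(1/n + 1/n):

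- n = 26 per group: sqrt(2/26) = 0.277; 0.4/0.277 = 1.44; 1.44 − 1.96 = −0.52; power about 30%.
- n = 51 per group: sqrt(2/51) = 0.198; 0.4/0.198 = 2.02; 2.02 − 1.96 = 0.06; power about 52%.

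A simulation of 4,000 data sets at each size gave 28% and 51%. The values 26 and 51 are the group sizes in section 2.4. Clustering by department would lower both figures.

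**Step 5: contexts.** Of the seven contexts in 2.10.3, three (training design, trainer behaviors, colleague support) are measured only after training. With acceptability from Table 3 it is four of eight. In three of the five Table 3 families, a context shares a survey with a mechanism:

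- family 3: colleague support with transfer;
- family 4: training design and acceptability with integration;
- family 5: trainer behaviors with voluntary participation and integration.

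**The case against.** The strongest reply is that the interaction can be fitted. Every between-group hypothesis in section 2.8.2 compares Group 1 with Group 2, so that is a natural reading of the intervention in 2.10.3, and the Limitations section already discloses the self-selection. This stands. A reader might infer that the moderation step cannot be estimated at all; the documents do not support that. Only the training-versus-no-training version is out of reach. Contrast coding may be left to an analysis plan, but no such plan can recover mechanism values that are never collected from untrained people.

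A reader might also infer that contexts and mechanisms are all rated at the same time. They are not. Four of the seven listed contexts are measured at T1. The workshop-day ratings precede training transfer by two weeks. The one-month repeat of the nine-item survey lets colleague support be lagged. Section 2.10.2 also treats concurrent colleague support as a deliberate kind of context. Nor would shared-method bias by itself create a false interaction: in its additive form it inflates main effects.

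Section 2.10.3 opens with a broader aim, contexts interacting with mechanisms to produce outcomes, which can be estimated among trained participants. The nine hypotheses do not depend on this step.

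Finally, the lack of a scale named for engagement with need crafting does not show that it goes unmeasured. A training-transfer item on applying need crafting strategies may capture it. If it means need crafting itself, that outcome has pre-training values. The point is therefore limited to mechanisms that have a named scale.

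**Conclusion.** The concern holds in this limited form. For all three mechanisms with a named scale there are no untrained observations, so moderation of a training-versus-no-training effect on them is not identifiable, and randomization of Groups 1 and 3 does not help. NC + NN versus NC only is the sole between-arm contrast for mechanisms. It is non-randomized, confounded with manager volunteering and specific to the added NN component. Under the assumptions shown, its power for an interaction of 0.4 is roughly 28% to 51% before clustering. Three of the seven listed contexts, or four of eight with Table 3, are post-treatment variables and not moderators of an intervention effect.

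The identifiability conclusion rests on the written schedule alone; the power figures rest on assumed values. The wording should be changed, because it affects what the realist analysis can claim. The main effect hypotheses are untouched.

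**What to change.** 1. **Moderation of the intervention effect.** Compare Group 1 with still-untrained Group 3 on need crafting, leader support and need satisfaction, keeping the department random effect. Use T4, where Group 1 is at one month and Group 3 completes the battery before its workshop (section 2.8.1). Add T3 only if sections 2.7 and 2.8.1 are reconciled: the first gives Group 3 a repeat of the pre-test battery at T3, while the second schedules its outcome instruments from T4. Limit moderators to readiness, communication, autonomy and workload, taken at T1 in both groups.
2. **Context-mechanism-outcome models in trained participants.** Label them associational and order them in time: T2/T4 training reactions, then T3/T5 transfer and proximal outcomes, then T4/T6 need satisfaction. Lag colleague support from T3/T5 to transfer at T4/T6. Adjust for the pre-training outcome.
3. **NC + NN versus NC only on mechanisms.** If reported, name the contrast and state that it is non-randomized.
4. **Engagement with need crafting.** Drop it as a separate mechanism or equate it with training transfer.

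The cost is wording and analysis specification; no new instrument is needed. Causal language becomes weaker, and item 1 tests moderation on outcomes, so it no longer tests the context-to-mechanism step itself. If Group 3's outcome battery does start only at T4, the T4 comparison also has no earlier Group 3 outcome to adjust for, which is a further reason to reconcile the two sections.

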#### Outcome measures

2.8.1

Evaluating the effectiveness of the intervention (i.e., proximal outcomes) will help to determine its success and whether the desired results have been attained. Proximal benefits refer to shorter-term, more immediate, subjective benefits experienced or observed, often as a direct cause of the intervention (i.e., differences in need crafting behavior and perceived managerial support). By contrast, distal outcomes are usually only noticeable over a more extended period of time and often more indirectly as a result of proximal benefits (i.e., changes in need satisfaction).

On the day of training, but before the need crafting workshop starts, participants will need to complete an outcome measure to determine their degree of need crafting, current need satisfaction, and perceived need-support from their immediate managers. The three measuring instruments to be used for the effect evaluation are discussed below (De Angelis et al., 2020). These instruments were selected for their direct alignment with the constructs in the intervention’s program theory and their operationalization, as well as for their explicit grounding in SDT. The adapted NCS operationalizes the proximal outcome targeted by NC (need crafting) and has been validated in the South African work context (Putter et al., 2024). The TMIB-S operationalizes the proximal outcome targeted by NN (perceived need-supportive managerial behaviors) and was developed and validated from an SDT perspective (Huyghebaert-Zouaghi et al., 2023). The single-item need satisfaction scales capture the distal outcome (basic psychological need satisfaction) while minimizing respondent burden across repeated measurement waves, with validity and reliability comparable to multi-item scales (Martela and Ryan, 2026).

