The first instrument will be an adapted version of the Need Crafting Scale (NCS) (Laporte et al., 2021), comprising nine items. The original scale was adapted by Putter et al. (2024) to better suit the work context by making small changes to the instructions as well as the wording of items (i.e., references to “in their lives” were changed to “at work,” and “people” were replaced with “colleagues”). Only the three action-oriented items of each subscale will be administered, while the negatively phrased items will be omitted. Previous research found no significant value added from the negatively phrased items, as these items did not load significantly onto their *a priori* factors when controlling for the method factor (Putter et al., 2024). These nine items will be rated on a five-point Likert scale, ranging from 1 (completely not true/disagree) to 5 (completely true/agree). Examples of the items include “*I deliberately choose activities I am good at*” (competence crafting action), “*As much as possible, I try to do things that I really want to do rather than things that have to be done*” (autonomy crafting action), and “*Even when I feel lonely, I still try to contact colleagues who care for me*” (relatedness crafting action).

The second instrument will be the Tripartite Measure of Interpersonal Behaviors-Supervisor (TMIB-S), comprising 22 items, which will measure need-oriented leader behaviors (Huyghebaert-Zouaghi et al., 2023). However, only the “need-supportive behaviors” subscale that comprises eight items will be used to determine the degree to which managers are perceived as supportive following the intervention. Examples of items include “*My supervisor shows that they understand my perspective*” (autonomy support), “*My supervisor recognizes my efforts and accomplishments*” (competence support), and “*My supervisor shows care and concern*” (relatedness support). The need-supportive behaviors subscale will be answered through a seven-point Likert scale, ranging from 1 (strongly disagree) to 7 (strongly agree) (Huyghebaert-Zouaghi et al., 2023). These three instruments will be administered at T2 to T4 (Groups 1 and 2) and T4 to T6 (Group 3).

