The last instrument will be the Single-Item Scales for Basic Psychological Need Satisfaction, comprising three items (Martela and Ryan, 2026). These items are “*I am able to do things that I really want and value at work*” (autonomy), “*I can do things well and achieve my goals*” (competence), and “*I feel close and connected with other colleagues who are important to me*” (relatedness). This three-item scale was found to be valid and reliable with strong comparability to multi-item scales. Items will be measured on a seven-point Likert scale, ranging from 1 (very strongly disagree) to 7 (very strongly agree) (Martela and Ryan, 2026).

These same three instruments, as discussed above, will be administered during the 2-weeks reflection meeting held with participants as well as 1 month after the intervention training. These outcome measures will form part of the post-test and will be administered separately to all three groups at different times (first to Group 1 and 2 and then to Group 3) in order to determine the potential changes within each group as well as measure any possible differences between the groups. Each group will undergo two separate post-tests, with all post-testing occurring between T3 and T6 (see Figures 1, 2).

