Based on theoretical proximity to training content and previous research, the largest between-group differences were expected for perceived need-supportive leadership (the direct target of the leader intervention), followed by need satisfaction (downstream of both crafting and leader support), with more modest effects anticipated for need crafting behaviors (since both groups directly received crafting training).

In the intervention study, linear mixed-effects models (LMMs) will be used to evaluate the effects of interventions on need crafting behaviors, need satisfaction, and need-supportive leader behaviors (i.e., to test these hypotheses). LMMs are ideal for this design because they handle repeated measures (pre-test, post-test, and follow-up) and account for the nesting of participants within departments, addressing both individual and group-level variability. By modeling random effects for participants and departments, LMMs ensure that differences in responses over time and between groups are properly accounted for. Additionally, LMMs effectively manage missing data, allowing us to test interaction effects between time and group and providing a robust evaluation of intervention outcomes across multiple levels (e.g., Snijders and Bosker, 2012).

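### The mediation chain in Section 2.10.3 is not conditioned on the pre-workshop scores the study collects; fitted on post-training levels, it can appear with no training effect

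*Protocol article*

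**What the plan says.** Section 2.10.3 (Statistical integration plan) describes two linked steps. Moderation models test whether contextual variables "influence the strength of relationships between the intervention and mechanisms". Then "mediation models will be used to examine whether mechanisms predict proximal outcomes (need crafting behaviors and perceived leader support), which then lead to"; that chain ends in need satisfaction. The text does not say which wave each score comes from, whether levels or changes are analysed, or which covariates enter.

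The timing comes from other sections:

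- **Outcomes before training.** Section 2.8.1: "On the day of training, but before the need crafting workshop starts, participants will need to complete an outcome measure", covering need crafting, need satisfaction and perceived manager support.
- **Outcomes after training.** The same instruments "will be administered during the 2-weeks reflection meeting held with participants as well as 1 month after the intervention training".
- **Voluntary participation and integration (mechanisms).** Section 2.9.1.2: "This will be measured at T2 (for Groups 1 and 2) and T4 (for Group 3), directly after participants have received the intervention training".
- **Training transfer (mechanism).** Section 2.9.1.3: "Measured at T3 and T5, respectively", at the 2-week meeting, which is also the first post-test. It is repeated at 1 month (Section 2.9.1.4).

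For the effect models, Section 2.8.2 does bring in the pre-test. It chooses linear mixed models because "they handle repeated measures (pre-test, post-test, and follow-up").

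**The concern.** An employee who already crafted, already had a supportive manager or was already satisfied is likely to report more willingness and transfer after training, and to score higher on crafting and need satisfaction at every later wave. Regressions among post-training levels pick up these standing differences as mechanism-to-crafting and crafting-to-satisfaction paths. Spacing the waves does not help, because a stable difference is present at each of them.

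Randomizing departments to Group 1 or Group 3 does not help either. Mechanism scores exist only after training, so the chain compares trained people with one another, and they may have differed beforehand.

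This analysis carries the study's account of how and why the intervention works (Sections 2.10 and 2.10.1). An error here would run towards confirming the program theory.

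**Working it through.** **The plan's own figure.** The article gives no sample size or expected effect for the mediation analysis. Section 2.4 gives 26 and 51 per group. They serve here only to set plausible totals over three groups: 3 × 26 = 78 and 3 × 51 = 153.

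**Null model (assumed).** Mechanism M is measured once, after training. Proximal outcome P and distal outcome D are each measured before (P0, D0) and after (P1, D1). Every score has variance 1, of which a share s is stable. The stable parts correlate c between constructs; the rest is independent occasion noise. Training changes nothing. The documents give neither s nor c.

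**Step 1: size of the spurious chain on post-training levels.** Any two different constructs correlate r = s × c. The M-to-P path is r. The P-to-D path given M is (r − r²)/(1 − r²) = r/(1 + r). The spurious indirect effect is therefore r²/(1 + r):

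- s = 0.5, c = 0.3: r = 0.15, so 0.0225/1.15 = 0.020
- s = 0.5, c = 0.5: r = 0.25, so 0.0625/1.25 = 0.050
- s = 0.7, c = 0.3: r = 0.21, so 0.0441/1.21 = 0.036
- s = 0.7, c = 0.5: r = 0.35, so 0.1225/1.35 = 0.091
- c = 0: r = 0, so 0

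The simulated means agree with these values.

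**Step 2: how often it is declared significant.** Simulation of 2,000 runs per cell. The chain counts as found when M-to-P and P-to-D given M both have two-sided p < 0.05. In this table the adjusted analysis puts P0 and D0 in both paths. Results at n = 153:

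| s | c | Post-training levels | Adjusted for P0 and D0 | Change scores in P and D |
|---|---|---|---|---|
| 0.5 | 0 | 0.5% | 0.4% | 0.2% |
| 0.5 | 0.3 | 14% | 1% | 0.4% |
| 0.5 | 0.5 | 62% | 5% | 0.4% |
| 0.7 | 0.3 | 41% | 1% | 0.2% |
| 0.7 | 0.5 | 90% | 4% | 0.2% |

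A separate simulation covered s from 0.5 to 0.7 and c from 0.3 to 0.5. On post-training levels it gave about 5-54% at n = 78 and 16-90% at n = 153. With pre-workshop scores added it gave about 1-7%. Its lower end at n = 153 differs from the table's 14% only by simulation error.

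**Step 3: why adjustment does not reach zero.** P0 measures the stable part of P with error, and M has no pre-training score. With P0 in the model, the M-to-P path under the null is sc(1 − s)/(1 − s²c²):

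- s = 0.5, c = 0.5: 0.125/0.9375 = 0.13, down from 0.25
- s = 0.7, c = 0.5: 0.105/0.8775 = 0.12, down from 0.35

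In the extreme case c = 0.7 at n = 153, 12-16% of null runs still show the chain with P0 and D0 in both paths, against 89-99% unadjusted.

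**Limit.** The simulations ignore clustering by department.

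**The case against.** A reader might infer that the plan leaves the pre-workshop scores out of the mediation, or works on raw post-training levels. The text does not say so. An article condenses the plan, and the covariates of a secondary model are often settled in a fuller document. Section 2.8.1 also describes the proximal outcomes as differences and the distal outcome as changes. If the chain is fitted on change scores, the false chain appears in at most 0.4% of null runs in every cell simulated. This stands: the concern is conditional on how the models are fitted.

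A reader might also infer that the intervention is absent from the analysis. It is not, since the preceding sentence of Section 2.10.3 links the intervention to the mechanisms. But those mechanisms have no scores from untrained people, so that link cannot rest on a trained-versus-untrained contrast.

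The magnitude rests wholly on assumed correlations, and at zero cross-construct correlation the problem disappears. That stands too, so a false chain is likely rather than certain. A zero correlation is hard to defend here, though: the program theory itself ties crafting, support and satisfaction together, and Section 3.1 concedes common method bias across all measures.

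Finally, the context-mechanism-outcome work is framed as exploratory, H1 to H3 are tested by other models, and sensitivity analyses are promised. This limits the damage to the mechanism conclusions. The content of the sensitivity analyses is not given.

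**Conclusion.** The point holds in conditional form. Section 2.10.3 states the direction of the chain but does not tie it to pre-workshop scores that are already collected. Run on post-training levels, it would be a weak test of the program theory. A false chain would appear in roughly 5-54% of null trials at n = 78 and 16-90% at n = 153, against about 1-7% with pre-workshop scores.

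These figures assume stable shares of 0.5 to 0.7, cross-construct correlations of 0.3 to 0.5, and no clustering. The totals are multiples of the power-analysis minima, not a stated mediation sample.

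The effect hypotheses H1 to H3 are not affected. What is at stake is whether the mechanism findings can be believed. Even after adjustment they cannot be read as the route of the intervention effect, because some bias remains and untrained employees have no mechanism scores.

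**What to change.** In Section 2.10.3, state that:

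1. the mechanism-to-proximal path adjusts for the pre-workshop score of that proximal outcome;
2. the proximal-to-distal path adjusts for the pre-workshop scores of both that proximal outcome and need satisfaction;
3. the chain is reported as an association among trained employees, not as the route of the intervention effect.

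Taking mechanism, proximal and distal scores from successive waves would also help, but is not enough alone. If change scores are what is meant, the section should say so.

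The cost is a few sentences of analysis text and no new data. The downside is that estimated indirect effects will be smaller.
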